**Methods:**

The digital health system intervention will provide automatic measurement of medication adherence via smart labels for pill bottles or injectors as well as a monitoring platform for providers. The system will prompt patients to complete a two-item assessment of symptoms monthly using the PRO-2 scales for UC and Crohn disease, from which increased symptoms will be alerted to providers. Participants will be randomized 2:1 to the intervention group or the control group, which will receive standard of care. All participants are required to complete questionnaires at baseline as well as at 12, 26, and 52 weeks. Assuming an adherence rate of 0.65 and 0.9 among control and intervention participants, respectively, we will need to enroll 123 participants: 82 (66.7%) in the intervention group and 41 (33.3%) controls. We will compare adherence as measured by the medication possession ratio, defined as the number of days of supply of medication obtained during the observation period out of the total number of days in the observation period, in participants using the RTM versus those receiving standard of care. We will also compare clinical outcomes and health care use in participants using the RTM versus those receiving standard of care.

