### Statistical Analyses

Baseline analyses will include tabulations of demographic and clinical variables of the study participants. Chi-square tests and 2-tailed *t* tests will be used to compare these groups to determine whether baseline differences exist. The distribution of each continuous variable will be inspected for outliers to determine whether a parametric or nonparametric approach should be applied. The Wilcoxon rank sum test will be used for any variable that does not meet the statistical assumptions of the *t* test. In addition, analyses will be conducted stratified by clinical site to determine whether the sites are comparable across the groups of interest. If differences are detected, these variables will be evaluated as potential confounders in the regression models.

For study aim 1, we will compare the mean MPR ratio between the intervention and standard of care groups using *t* tests. For study aim 2, we will compare differences in health care use between the groups using the Wilcoxon ranked sum test because we expect that the data will not be normally distributed.

For the secondary aims of clinical outcomes and health care use, dichotomized outcomes will be compared in a similar fashion with bivariate analyses. For health care use, the outcome will be investigated in quartiles of health care use, and specific outcomes of interest selected a priori will be investigated (eg, need for hospitalization for IBD, need for IBD surgery, and initiation of corticosteroids).

All analyses will be completed using intention-to-treat principles. Assuming 2 intervention participants for every 1 control, with adherence rates of 0.65 among controls and 0.9 in intervention participants and with a type I error rate of 0.05 and power of 0.9, we will need to enroll 123 participants: 82 (67%) in the intervention group and 41 (33%) controls. We may enroll more patients pending our initial recruitment and data capture.

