Although we will make every effort to obtain complete data from all randomized participants, we anticipate that there could be as much as 20% loss to follow-up by 12 months. To detect potential bias by analysis of only the collected data, we plan first to compare patients with data with those without data at a given time point on baseline characteristics to determine characteristics of those who do not provide complete data. We will also perform sensitivity testing to see whether estimates of intervention effects differ if only patients with complete data are analyzed. Depending upon the extent of missingness, we will also consider imputation methods that use multiple regression predictions for imputation.

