### Few Difficulties or Limitations Anticipated

We anticipate few difficulties or limitations in conducting the proposed study. Enrollment of 123 participants over 12 months among 5 sites (approximately 2 per site per month) is a very reasonable goal as each site is a large referral center for the care of patients with IBD. In addition, we are not restricting enrollment to patients initiating treatment with a biologic or small molecule, which will increase the pool of eligible patients. If recruitment is challenging, we can recruit additional sites to participate. We have included sites in the Northeast, mid-Atlantic, Midwest, and South, which should increase the diversity of the patient population studied. However, because IBD is underrepresented in populations consisting of people of color, our participants will not be as diverse as the general population at each site. Moreover, a digital platform may not benefit disadvantaged people with limited access to technology or technological literacy. Finally, although the COVID-19 pandemic seems to be easing, it is possible that new variants of the virus will emerge, resulting in restricted access for in-person visits. We do not anticipate that prescribing patterns will change if this occurs, and we have implemented remote consent and data collection to mitigate these barriers to enrollment and capture of outcome data.

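### The enrolment target of 123 is the zero-loss sample size: it holds no allowance for the loss of up to 20% that the plan anticipates, and on the plan's own two-proportion calculation power at that loss is about 83%, not 90%

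*Protocol article*

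**What the plan says.** The sample-size statement in Statistical Analyses allocates 2:1 in favour of the intervention and takes "adherence rates of 0.65 among controls and 0.9 in intervention participants". The significance level is set at 5% and the power at 90%. The conclusion drawn is that "we will need to enroll 123 participants: 82 (67%) in the intervention group and 41 (33%) controls". A closing sentence adds that more patients might be enrolled, depending on early recruitment and data capture. It gives no number and does not mention attrition.

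The Abstract (Methods) repeats the target: "we will need to enroll 123 participants: 82 (66.7%) in the intervention group and 41 (33.3%) controls". The Discussion (Few Difficulties or Limitations Anticipated) judges feasibility on the same number: "Enrollment of 123 participants over 12 months among 5 sites (approximately 2 per site per month) is a very reasonable goal".

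The paragraph after the sample-size statement says "we anticipate that there could be as much as 20% loss to follow-up by 12 months". It plans to compare participants with and without data, to run a sensitivity analysis on complete data, and to consider regression-based imputation depending on how much is missing.

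**The concern.** A power calculation of this kind returns the number of participants who must have an outcome. Enrolment has to be larger by whatever fraction is expected to be lost. Here one number appears to serve as both, and the plan's own attrition figure follows directly after it.

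If 123 holds no allowance, the stated 90% power applies only if nobody is lost, which the plan does not assume. A null result would then be read against a power that the design lacks under its own assumptions. At 20% loss, the chance of missing the planned effect would be about 17% instead of 10%.

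**Working it through.** **Inputs, all from Statistical Analyses.** Control rate 0.65, intervention rate 0.90 (difference 0.25), allocation 2:1, type I error 0.05, power 0.90, enrolment 82 + 41, loss up to 20%. Sidedness is not stated for the sample size. I take it as two-sided, because only the two-sided version reproduces the plan's number and because for the baseline comparisons the plan says "2-tailed *t* tests will be used to compare these groups".

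**Step 1: reproduce 123.** Pooled-variance two-proportion formula, no continuity correction, no dropout.

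- Mean rate p = (0.65 + 2 × 0.90)/3 = 0.8167, so p(1 − p) = 0.1497.
- Controls n = [1.960 × √(0.1497 × 1.5) + 1.2816 × √(0.65 × 0.35 + 0.90 × 0.10/2)]² / 0.25²
- = [1.960 × 0.4739 + 1.2816 × 0.5220]² / 0.0625 = 1.5978² / 0.0625 = 40.85, rounded up to 41.
- Intervention: 2 × 41 = 82. Total 123, an exact match.

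Other versions of the formula do not fit with or without an allowance. Before any dropout, the two-sided unpooled version gives 138, two-sided with continuity correction 141, one-sided 102, and one-sided with continuity correction 120. The two-sided arcsine version gives about 122, which also leaves no room for loss.

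**Step 2: is an allowance hidden in 123?** No. Allowing for 20% loss would give 123/0.8 = 153.75, so 154.

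**Step 3: power when some are lost.** Power = Φ[(0.25 − 1.960 × SE₀)/SE₁], with SE₀ = √[p(1 − p)(1/n₁ + 1/n₂)] and SE₁ = √[0.2275/n₁ + 0.09/n₂], where n₁ is controls and n₂ is intervention.

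- No loss (41 and 82): SE₀ = 0.0740, SE₁ = 0.0815, z = 1.287, power 0.901.
- 20% loss (33 and 66 after rounding): SE₀ = 0.0825, SE₁ = 0.0909, z = 0.972, power 0.834.

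| Loss | Controls / intervention with data | Power |
|---|---|---|
| 0% | 41 / 82 | 0.901 |
| 5% | 38.95 / 77.9 | 0.887 |
| 10% | 36.9 / 73.8 | 0.871 |
| 15% | 34.85 / 69.7 | 0.853 |
| 20% | 32.8 / 65.6 | 0.832 |

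Rounding the 20% row to whole participants gives 0.824 to 0.834. Exact binomial power for the uncorrected test moves from 0.910 at 41/82 to 0.851 at 33/66, a similar drop.

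**Step 4: enrolment that would match.** 123/0.8 = 153.75, so about 154. In whole 2:1 sets, 41/0.8 = 51.25 rounds up to 52, giving 52 + 104 = 156.

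**Step 5: what this says about the primary test.** The primary outcome is the difference in mean MPR, compared by t test, and no standard deviation is given. Assume, for illustration only, a mean difference of 0.25 and a two-sided t test with 33 and 66 participants. Power is then 0.996 at SD 0.25, 0.972 at 0.30, 0.913 at 0.35 and 0.827 at 0.40. It passes below 90% at an SD of about 0.36. The 83% therefore cannot be carried over to the primary analysis.

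**The case against.** Five points can be made for the plan.

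- **The 20% is a ceiling, not a forecast.** This stands: 83% is the power at that bound. But power is already below 90% at 5% loss, so the missing allowance does not depend on the bound being reached. The article's own 12-month precedents lost more: 29 of 47 participants completed the ulcerative colitis home telemanagement trial and 259 of 348 (74.4%) the text-message telemedicine trial.
- **Someone lost by 12 months may still have supplied data.** Medication fills are reported at weeks 12, 26 and 52, so a participant lost after week 26 has given about half a year of MPR information. This also stands: treating every lost participant as contributing nothing is the pessimistic case. The plan states intention-to-treat principles but gives no rule for partial MPR data, and imputation is only to be considered. Recovery is possible, not secured.
- **More patients may be enrolled.** That option has no number and is not tied to attrition, and both the Abstract and the feasibility paragraph work from 123. It is not an allowance.
- **The primary analysis is a t test on means.** This is the strongest point. A reader might infer that the trial's real power is 83%, or that its primary comparison is underpowered. The documents do not support either reading: without a standard deviation, that power could lie well above or below 90%.
- **A journal article condenses.** True, but this is not an omitted detail. Both figures are printed, one paragraph apart, and they do not fit the stated power together.

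**Conclusion.** The point holds. The figure of 123 is the zero-loss sample size from the plan's two-proportion calculation, used as the enrolment target in three places, with no allowance for the loss that the plan anticipates. On that calculation, power falls from 0.901 to about 0.89 at 5% loss, 0.87 at 10% and 0.83 at the 20% upper bound.

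This rests on three assumptions: a two-sided test, loss spread equally across the arms, and no outcome information from those lost. The first is supported by the exact match to 41 and 82. The third makes 83% the lower end for losses up to 20%.

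The finding concerns the stated power and its link to enrolment. It does not show that the primary t test lacks power, that 20% will be lost, or that the trial must enrol more.

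**What to change.** In the Abstract (Methods) and in Statistical Analyses, state that 123 (82 + 41) is the number needed with outcome data. Add that, with 123 enrolled, the power of the two-proportion calculation for 0.65 against 0.90 is about 83% if loss reaches 20% and those lost contribute no outcome. Label it explicitly as the power of that calculation and not of the t test on mean MPR. In Few Difficulties or Limitations Anticipated, make clear which of the two numbers the recruitment pace refers to.

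If the sponsor chooses to use its stated option to enrol more, the figure that keeps 90% on the same calculation at 20% loss is about 154, or 156 in whole 2:1 sets. That is a choice and not part of the correction.

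The cost is a few sentences and a less favourable stated power. The correction itself changes no enrolment, procedure or analysis.

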We then pursued a 12-month randomized clinical trial to assess the effectiveness of the UC HAT system compared with best available care (BAC). We modified the symptom diary and alert criteria to make them specific to UC and added action plans and electronic messaging for participants to communicate with the research team. Adults with UC from the University of Maryland and Veterans Affairs Hospital in Baltimore were randomized to self-testing with the UC HAT system weekly or BAC. All participants underwent visits at baseline and every 4 months. Disease activity was measured using the Seo index [18,19], disease-specific QoL was measured using the Inflammatory Bowel Disease Questionnaire [20], and medication adherence was measured using a medication adherence scale [21]. We randomized 47 patients, and 29 (62%) completed the study. After adjustment for baseline QoL scores, participants in the UC HAT arm had a strong trend toward decreased Seo index scores from baseline (mean –11.9, SD 6.6; *P*=.08). Furthermore, after adjustment for baseline disease knowledge, participants in the UC HAT arm had a significant increase in QoL scores from baseline (mean 12.5, SD 5.9; *P*=.04), whereas participants in the BAC arm had nonsignificant decreases in QoL scores from baseline (mean –3.8, SD 5.3; *P*=.47). The difference in change in QoL scores from baseline between the UC HAT and BAC arms at 12 months was significant. Self-reported adherence to medical therapy was low in both groups at baseline (BAC: 45% and UC HAT: 40%). Adherence rates increased in both groups but were not significantly different at any time point after baseline. Both arms had poor IBD knowledge at baseline, with improvement at the 12-month follow-up; however, there was not a significant difference between the UC HAT and BAC arms at the 12-month follow-up [22]. Our results suggested that the randomization process was inadequate because participants in the UC HAT arm had higher rates of immune suppression use and greater impairments in QoL than participants in the BAC arm. We suspect that the baseline differences in favor of the BAC arm impaired our ability to demonstrate a treatment effect of the UC HAT system. This hypothesis is supported by the findings of clinically important improvements in disease activity and QoL from the baseline to the 12-month visit in the UC HAT arm. Furthermore, after adjustment for baseline disease knowledge, a significant improvement in QoL was noted in the UC HAT participants.

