
#### Telemedicine for Patients With IBD

We then conducted a multicenter randomized controlled trial to assess the effectiveness of telemedicine for patients with IBD (TELE-IBD) weekly (TELE-IBD W) or every other week (TELE-IBD EOW) compared with BAC. Patients completed self-assessments via SMS text messages, assessment of weight was completed through use of an electronic scale and manually entered by the participant, and educational messages were sent either weekly or twice weekly throughout the trial. We recruited 348 participants (n=116, 33.3%, TELE-IBD W; n=115, 33%, TELE-IBD EOW; and n=117, 33.6%, BAC controls), including 236 (67.8%) participants with CD and 112 (32.2%) with UC or indeterminate colitis. Of the 348 participants, 259 (74.4%) completed the final 12-month visit. Clinical indices of CD activity using the Harvey-Bradshaw Index (HBI) decreased in the control, TELE-IBD EOW, and TELE-IBD W groups (*P*=.16). The decreases in HBI scores over time were significant in all groups (*P*<.001) but not different among the groups (*P*=.18). Clinical indices of UC activity using the Simple Clinical Colitis Activity Index (SCCAI) decreased in the control, TELE-IBD EOW, and TELE-IBD W groups (*P*=.41), but they were significant only in the controls (*P*=.01) and not different among the groups (*P*=.25). IBD QoL scores increased in the control, TELE-IBD EOW, and TELE-IBD W groups (*P*=.42) but were significant only in the TELE-IBD EOW group (*P*=.03) and not different among the groups (*P*=.95). However, use of health care resources was different among the groups, with participants in the TELE-IBD arms experiencing lower total and IBD-related hospitalization rates and higher number of noninvasive diagnostic tests, telephone calls, and electronic messages [23]. In addition, those in the TELE-IBD arms had a greater improvement in Crohn’s and Colitis Knowledge scores [24] than those in the standard of care group. General self-efficacy scores improved in all arms during the trial but were not different among the groups [25,26]. In an analysis of intervention participants only, adherence increased with depressive symptoms in those who were aged ≤40 years (*P*=.02), but there was no association between depressive symptoms and adherence in those who were aged >40 years (*P*=.53) [27]. A follow-up qualitative study demonstrated that participants identified clear benefits of the TELE-IBD system, including a better understanding of the disease process, monitoring of symptoms, and feeling of connection to the health care team. Both adherent and nonadherent participants preferred a flexible system that was personalized, included targeted education, and promoted self-management [28].

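### The enrolment target of 123 is the zero-loss result of the plan's own calculation: its 90% power falls to about 83% at the 20% loss the plan allows for

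*Protocol article*

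**What the plan says.** The relevant statements stand in adjacent paragraphs of the protocol article, under Statistical Analyses.

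- **Sample size.** From adherence rates of 0.65 (control) and 0.90 (intervention), 2:1 allocation, and "with a type I error rate of 0.05 and power of 0.9", the plan concludes that "we will need to enroll 123 participants: 82 (67%) in the intervention group and 41 (33%) controls". The Abstract and the section on anticipated difficulties also use 123 as the number to enrol.
- **Expected loss.** The next paragraph states: "we anticipate that there could be as much as 20% loss to follow-up by 12 months". Twelve months is also the horizon of the primary outcome, mean MPR over the study (Outcomes and Outcome Measures).
- **Related provisions.** The sample-size paragraph keeps open an option to enrol more, depending on early recruitment and data capture, with no number attached. The missing-data paragraph says that, depending on how much is missing, "we will also consider imputation methods that use multiple regression predictions for imputation".
- **Earlier experience.** In the team's multicentre telemedicine trial, of 348 randomised, "259 (74.4%) completed the final 12-month visit". In the earlier home-telemanagement trial: "We randomized 47 patients, and 29 (62%) completed the study".

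**The concern.** A power calculation gives the number that must be analysed. The number to enrol equals it only if nobody is lost. If 123 is the analysable number and up to a fifth of it may be lost, the stated 90% does not describe the trial at the loss the plan itself allows for. A reader, funder or ethics board would take the risk of missing the assumed effect to be 10%. On the same assumptions it is about 17% at the 20% bound.

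**Working it through.** **Inputs** (Statistical Analyses unless stated)

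- p₁ = 0.65 (control), p₂ = 0.90 (intervention), difference 0.25
- Allocation 2:1, type I error 0.05, power 0.90
- Loss: up to 20%
- Two-sided testing is an assumption. The sample-size sentence does not state sidedness, and the only mention of two tails concerns baseline comparisons: "Chi-square tests and 2-tailed *t* tests will be used to compare these groups". The assumption is supported because it reproduces the plan's figure exactly.

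**Step 1: reproduce 123**

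Pooled proportion: p̄ = (0.65 + 2 × 0.90)/3 = 0.8167, so p̄(1 − p̄) = 0.1497.

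Controls needed = [1.960 × √(0.1497 × 1.5) + 1.282 × √(0.65 × 0.35 + 0.90 × 0.10/2)]² / 0.25²
= (0.9288 + 0.6690)² / 0.0625 = 40.85, rounded up to 41.

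Intervention = 2 × 41 = 82, total 123. This matches the plan with nothing left over for loss. Power at 41 + 82 is 90.1%. The arcsine formula also gives 123. The continuity-corrected and unpooled two-sided versions give 141 and 138.

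**Step 2: power after loss**

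Power = Φ[(0.25 − 1.960 × SE₀)/SE₁], where SE₀ uses the pooled proportion and SE₁ the separate ones.

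At 20% loss, 123 × 0.8 = 98.4 (32.8 controls, 65.6 intervention):

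- SE₀ = √[0.1497 × (1/32.8 + 1/65.6)] = 0.0827
- SE₁ = √(0.2275/32.8 + 0.09/65.6) = 0.0911
- Power = Φ[(0.25 − 0.1622)/0.0911] = Φ(0.963) = 0.832

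| Loss | Source of the loss figure | Evaluable | Power |
|---|---|---|---|
| 0% | implicit in 123 | 123 | 90.1% |
| 20% | the plan's upper bound | about 98 | about 83% |
| 26% (259/348 retained) | earlier multicentre 12-month trial | 91–92 | about 80–81% |
| 38% (29/47 retained) | earlier two-centre 12-month trial | about 76 | about 74% |

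The 20% result changes little with the formula: arcsine gives 82.9%, and Fisher's exact test about 80–81% (against 88.9% with all 123).

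**Step 3: enrolment that would keep 90% at 20% loss**

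123/0.8 = 153.75, so 154. Rounding by arm: 41/0.8 = 51.25 and 82/0.8 = 102.5, so 52 + 103 = 155.

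**Step 4: could 123 already include an allowance?**

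A one-sided calculation gives 34 + 68 = 102, and 102 × 1.2 = 122.4 also rounds up to 123. The article mentions neither a one-sided test nor an inflation. That route would also inflate incorrectly, since 102/0.8 = 127.5, so 128. The direct two-sided match is the plainer reading.

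**The case against.** Several objections have force.

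- **The 20% is a ceiling.** This stands. For any loss between none and 20%, power on the plan's rates lies between 90% and 83%. The 83% is the value at the bound, not a forecast.
- **Lost by 12 months does not mean unevaluable.** This stands in part. Fill dates and days' supply are reported at weeks 12, 26 and 52, so someone who leaves after week 26 has already contributed MPR data. The plan also treats the complete-data analysis as a sensitivity check. Counting 98 evaluable ignores this partial information. But the plan does not count it either, and does not say how it enters the primary comparison.
- **More participants may be enrolled.** The option has no number and is not tied to attrition, so it is not an allowance.
- **The earlier trials were run differently.** They used weekly or fortnightly self-testing and follow-up visits, whereas here outcomes are captured electronically without visits. So 26% and 38% show only that 20% is not a cautious figure. They do not predict loss in this trial.

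Three stronger readings are tempting, and the documents do not support them.

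1. **That the trial's true power is 83%.** The planned primary analysis is a t test on mean MPR, and the article gives no SD. For a 0.25 difference, an assumed SD of 0.40 gives 90% falling to 83% at 20% loss, while an assumed SD of 0.30 gives 99% falling to 97%. The mismatch between calculation and test is a separate matter.
2. **That the planned imputation would inflate the type I error.** That needs single, deterministic predictions entered as if observed. The article says only that regression-based methods will be considered, wording that proper multiple imputation would also fit.
3. **That the arithmetic behind 123 is wrong.** It is correct, but the result is labelled as the number to enrol when it is the number to analyse.

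**Conclusion.** The point holds as a statement that is wrong as written. The target of 123 is the evaluable number of the plan's own calculation, and the expected loss in the next paragraph is not carried into it. On those assumptions, power is about 90% only with no loss. It is about 83% at the 20% bound and about 80–81% at the 26% loss of the earlier multicentre trial.

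This rests on two-sided testing, equal proportional loss in both arms, no credit for partial data, and the plan's rates of 0.65 and 0.90 treated as proportions. No bias in the primary estimate follows from it. The consequence is a stated power that is too favourable by up to about 7 percentage points at the plan's own bound.

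**What to change.** **Needed.** In Statistical Analyses, restate the power along these lines: about 90% if all 123 are evaluable, falling to about 83% with 20% loss (about 98 evaluable). Say that these figures refer to the comparison of two proportions and not to the planned t test on mean MPR. Showing the 26% case alongside would be informative. Where the Abstract repeats the target, it should be consistent with this.

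**Optional.**

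- Use the week-12 and week-26 fill reports of participants lost later in the main analysis, through multiple imputation with arm in the model. Complete cases then remain the sensitivity analysis, as the plan already has them.
- If the option to enrol more is used, base the decision only on the pooled count of evaluable participants, without sight of results by arm.

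**Cost.** Wording only, and a less favourable stated power. No extra participants are required. If the sponsor prefers to keep 90% at 20% loss, the target becomes 154 (155 with rounding by arm), which is 31 to 32 more than planned.
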